### Sample Size and Power Calculations

Primarily, our objective is to compare the proportion of subjects with mild to moderate depression in the intervention and control arms 6 months after the end of treatment. Based on results from our pilot project, we assume that the difference in proportion of depression cases at 6 months follow-up between intervention (15%) and control arms (25%) would be 10%. Using formulae proposed by Hayes and Moulton [48], and assuming the between-cluster coefficient of variation *k* of .25, a study with 12 nonmatched pairs of clusters, and a cluster size of 32 PLWH (total expected sample size of 768 PLWH) would have 80% power of detecting a 10% reduction in major depression cases at the 5% significance level. Table 2 illustrates the sample size and power calculations for various assumptions made. The number of clusters has been increased to 15 pairs to allow for individual level analyses using multilevel random effects regression models, and the cluster size was increased to 40, accounting for a potential 20% loss to follow-up.

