#### Participant Eligibility Criteria, Recruitment, and Masking

To be eligible for the study, PLWH had to be 19 years and older, diagnosed with major depression assessed with the MINI depression module [32], antidepressant naïve, using ART, and residing in the villages where the trained LHWs lived. Individuals with high suicide risk [33], a severe medical disorder such as pneumonia or active tuberculosis, psychotic symptoms, and hearing or visual impairment were excluded from the study.

On a given clinic day, project research assistants worked with primary care health workers of a participating PHC in the center’s HIV clinic. The primary care health worker gave a health talk on depression to clients in the waiting area. Clients who felt that they had experienced symptoms of depression described in the health talk were invited for further evaluations using the Luo version of the 20-item self-reporting questionnaire [34] and the MINI depression module. This procedure was repeated until a total of 40 PLWH diagnosed with major depression were obtained from a given PHC.

Clients diagnosed with major depression were approached by research assistants who explained study procedures, determined eligibility, and then obtained informed consent. Each client who gave informed consent received baseline assessments with a standardized questionnaire. Recruited participants from the same village were assigned to a trained LHW residing in or near their village to receive the intervention they had been trained to deliver (ie, either GSP or GHE).

By design, both experimental and control interventions were identifiable to participants but will be masked to outcome assessors, the Data and Safety Monitoring Board, and data analysts.

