**Process evaluation outcomes**								
	Indicators of feasibility	The proportion of eligible participants who take up either intervention (Reach), the proportion who attended all 8 sessions of either intervention (dose delivered), and the proportion who are lost to follow-up (attrition) will be determined from the attendance registers		✓				
	Indicators of acceptability	A 9-item questionnaire [47] will assess participant’s satisfaction, the group facilitators’ knowledge and attitudes, and the participant evaluation of the intervention’s ability to reduce depression.			✓			
	Fidelity	A semistructured self-administered questionnaire completed by group facilitators will assess whether or not the interventions were delivered as planned.		✓				
	Contextual influences	A semistructured self-administered questionnaire completed by group facilitators will assess any facilitators or barriers to intervention delivery that they observed during group sessions.			✓			
	Causal mechanisms	A semistructured interviewer-administered questionnaire will assess participant’s knowledge, skills, or assets acquired during and after the interventions, which will give an indication as to whether or not the interventions influenced targeted risk factors for depression.			✓			

**Table 2 table2:** Sample size and power calculations.

Alpha	Beta	*k*	Cluster size	Control group proportion	Intervention group proportion	Minimum clusters required	Resulting power
.01	.2	.25	32	0.25	0.15	18	0.808
.05	.2	.25	32	0.25	0.15	12	0.803
.01	.2	.25	40	0.25	0.15	16	0.818
.05	.2	.25	40	0.25	0.15	11	0.823
.01	.2	.25	32	0.3	0.15	10	0.842
.05	.2	.25	32	0.3	0.15	7	0.849
.01	.2	.25	40	0.3	0.15	9	0.851
.05	.2	.25	40	0.3	0.15	6	0.84

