## Results

The trial has been approved by the Makerere College of Health Sciences School of Health Sciences Research Ethics Committee, TASO, and the Uganda National Council of Science and Technology. A Data and Safety Monitoring Board has been put in place to monitor trial progress. A total of 1140 persons living with HIV have been recruited to the trial. An analysis of baseline and 6-month data is in progress.

The results of this trial will not only be presented at national and international conferences but also submitted for publication in peer-reviewed journals and as a report to the funding agencies.

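### The 80% power stated for 12 clusters per arm, and all eight powers in Table 2, take no account of the small number of clusters; the headline figure is about 77%, although the trial as run is adequately sized

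*Protocol article*

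**What the plan says.** The section on sample size and power takes 25% depressed in the control arm and 15% in the intervention arm at 6 months, citing the pilot project. It names the Hayes and Moulton formulae, "assuming the between-cluster coefficient of variation *k* of .25", and concludes that "a study with 12 nonmatched pairs of clusters" of 32 people each (768 in total) "would have 80% power of detecting a 10% reduction in major depression cases at the 5% significance level".

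Table 2 gives eight scenarios: alpha .01 or .05, cluster size 32 or 40, and control proportion 0.25 or 0.30 against 0.15. Each has a column headed "Minimum clusters required" and a resulting power. The headline row shows 12 clusters and 0.803. Since 12 × 2 × 32 = 768, the counts are per arm.

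The design is then raised to 15 clusters per arm so that multilevel random effects models can be used, and to 40 people per cluster to allow for 20% loss to follow-up. No power is given for 15 per arm. The Results section reports: "A total of 1140 persons living with HIV have been recruited to the trial".

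**The concern.** Health centers are the randomized units, so the precision of the comparison depends on a between-center variance estimated from few centers. A formula with normal quantiles treats that variance as known and overstates power, and the overstatement grows as clusters become fewer or alpha smaller. Table 2 goes down to 6 clusters per arm, and half of its rows use alpha .01.

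Two things are at stake. The stated power and minimum counts would be too favorable, which matters to anyone who reuses Table 2 to plan a similar trial. And a reader who wants to interpret a null result needs the power of the 15-per-arm design, which the article does not give.

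**Working it through.** **Inputs**, all from the sample size section and Table 2: p0 = 0.25, p1 = 0.15, k = 0.25, m = 32 per cluster, c = 12 per arm, alpha 0.05, target power 0.80. The article does not say whether the test is one- or two-sided. Two-sided reproduces the table; one-sided would give 0.879 in the headline row.

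**Step 1: reproduce the stated figure.**

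V = p0(1−p0)/m + p1(1−p1)/m + k²(p0² + p1²)

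= 0.1875/32 + 0.1275/32 + 0.0625 × (0.0625 + 0.0225)

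= 0.0098438 + 0.0053125 = 0.0151563

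Clusters per arm = (1.960 + 0.842)² × V/(0.10)² = 7.849 × 1.5156 = 11.896, rounded up to 12.

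Power at 12 = Φ(0.10/√(0.0151563/12) − 1.960) = Φ(2.814 − 1.960) = 0.803.

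This matches the article. The same formula reproduces the other seven rows, both the counts and the powers, to the printed decimals. The method behind Table 2 is therefore not in doubt.

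**Step 2: allow for estimating the variance.** Keep V and all inputs. Replace the normal reference by a two-sided t-test on cluster proportions with 2(c−1) degrees of freedom, and take power from the noncentral t with noncentrality (p0−p1)/√(V/c).

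- c = 12: 22 df, noncentrality 2.814, critical value 2.074, power **0.767**.
- c = 13: 24 df, noncentrality 2.929, critical value 2.064, power **0.802**.

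A rough check that puts c−1 in place of c in the normal formula gives 0.769 at 12 and 0.803 at 13.

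**Step 3: all rows of Table 2.**

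| Alpha | m | p0 v p1 | Stated clusters | Stated power | t power at stated clusters | Clusters for 80% (t) | t power there |
|---|---|---|---|---|---|---|---|
| .01 | 32 | 0.25 v 0.15 | 18 | 0.808 | 0.758 | 20 | 0.815 |
| .05 | 32 | 0.25 v 0.15 | 12 | 0.803 | 0.767 | 13 | 0.802 |
| .01 | 40 | 0.25 v 0.15 | 16 | 0.818 | 0.762 | 18 | 0.826 |
| .05 | 40 | 0.25 v 0.15 | 11 | 0.823 | 0.784 | 12 | 0.822 |
| .01 | 32 | 0.30 v 0.15 | 10 | 0.842 | 0.748 | 11 | 0.805 |
| .05 | 32 | 0.30 v 0.15 | 7 | 0.849 | 0.785 | 8 | 0.845 |
| .01 | 40 | 0.30 v 0.15 | 9 | 0.851 | 0.746 | 10 | 0.811 |
| .05 | 40 | 0.30 v 0.15 | 6 | 0.840 | 0.759 | 7 | 0.833 |

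The gap is 0.803 − 0.767 = 0.036 in the headline row and 0.851 − 0.746 = 0.105 in the worst row. One extra cluster per arm is enough in six rows. In the first and third rows it is not: 19 gives 0.788 and 17 gives 0.796, so 20 and 18 are needed.

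**Step 4: the design as run.** 15 per arm, 28 df, critical value 2.048, two-sided 5%, 25% v 15%, k = 0.25.

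- 32 analysed per cluster (40 less 20%): noncentrality 3.146, power **0.859**.
- 1140/30 = 38 recruited on average; 38 × 0.8 = 30.4 analysed; V = 0.315/30.4 + 0.0053125 = 0.015674; noncentrality 3.094, power **0.848**.

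**The case against.** The strongest objection is that 0.767 is itself an approximation. It is the power of a t-test on cluster proportions, whereas the Statistical Analyses section plans an individual-level mixed model with clusters as a random effect, a baseline depression covariate and permutation checks. The article fixes no degrees of freedom for that model. This stands, and the restated figures should be labeled accordingly. It does not rescue 0.803, because the formula behind that figure is also cluster-level and ignores the estimation of the variance.

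A second objection is that nothing was miscalculated: the stated inputs and the plain formula do give the stated outputs. That is true, and the fault is one of approximation. But a count labeled as the minimum for 80% power should reach 80%.

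Third, 12 per arm is only a step on the way to 15, and the uncertainty in k is larger than the correction. As an illustrative range, the plain formula at 12 per arm and m = 32 gives 0.853 at k = 0.20 and 0.745 at k = 0.30. Both points limit the importance of the finding. Neither corrects Table 2, and the reason given for 15 pairs is multilevel modeling, not a small-sample allowance.

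Finally, a condensed article may leave out the power at 15 per arm, and its inputs allow a reader to work it out. So that gap is not an error in itself, but the figure belongs in any correction.

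**Conclusion.** The point holds for the stated figures. Under the plan's own assumptions, 12 clusters per arm of 32 give about 77% power, not 80%, and 13 are needed. The other seven minimums give about 75% to 78%, against stated powers of 0.808 to 0.851. All the errors are in the favorable direction. The result assumes a two-sided test, equal cluster sizes, k = 0.25 and a cluster-level t reference with 2(c−1) df.

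Three stronger readings are not supported:

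- A reader might infer that the trial is underpowered. It is not on these assumptions: 15 per arm gives about 85% to 86%.
- A reader might carry 77% and 13 clusters over to the whole table, or add one cluster to every row. Those two figures belong to the headline row, and a flat addition of one still falls short in two alpha .01 rows.
- A reader might conclude that 1140 were enrolled instead of 30 × 40 = 1200 because screening ran on diagnosed cases ("This procedure was repeated until a total of 40 PLWH diagnosed with major depression were obtained from a given PHC") and eligibility and consent came afterwards. The article describes that order of steps but nowhere explains the difference of 60, and 38 per center is only an average. The effect on power is about one point (0.859 to 0.848).

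**What to change.** Restate the headline as about 77% power at 12 clusters per arm, with 13 needed for 80%.

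In Table 2, the powers at the counts now printed become, in row order, 0.758, 0.767, 0.762, 0.784, 0.748, 0.785, 0.746 and 0.759. The minimum clusters per arm become 20, 13, 18, 12, 11, 8, 10 and 7. If only the new minimums are shown, pair them with the powers in the last column of the table in the working, so that counts and powers correspond.

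Add one sentence with the power at 15 per arm for 25% v 15%, k = 0.25, two-sided 5%: about 86% with 32 analysed per cluster, or about 85% with 1140 recruited (mean 38 per center) and 20% loss. State that the test is two-sided and that these are cluster-level approximations to the planned mixed model. Give no reason for the enrolment of 1140 unless it is documented.

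The cost is one recalculated table and two or three sentences. There is no change to design, recruitment or analysis.

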### Data Collection and Management

Study participants in the intervention and control arms will be asked to complete an interviewer-administered face-to-face standardized questionnaire to collect data on primary and secondary outcomes at baseline (T0), after completion of their group treatments (T1), and 6, 12, 18, and 24 months after end of treatment (T2, T3, T4, and T5 respectively). All the completed survey questionnaires will be reviewed by a research team member for missing data and unusual responses. Data will be entered into an EpiData (version 3.1) database. Regular reports will be produced on (1) patient accrual and follow-up completion/retention in relation to goals and timeline, (2) the randomization process and group comparability on the balancing variables, (3) key baseline characteristics of the sample, by (blinded) group, related to the primary and secondary outcome variables and proposed effect modifiers and mediators, (4) intervention exposure and adherence, and (5) protocol violations. Any observed delays in these processes or data irregularities will be followed up and resolved in a timely manner.

The complete de-identified dataset of the trial will be publicly available when finalized. Details of the data and safety monitoring plan and the study governance structure are shown in the Multimedia Appendix 4.

### Statistical Analyses

We will assess randomization across the two arms by comparing sociodemographic characteristics and other potential confounding variables using chi-square for categorical variables, and *t* tests or other equivalent nonparametric tests, as appropriate, for continuous variables. Primary outcomes will be the difference in follow-up proportions of participants who meet MINI criteria for major depression and difference in follow-up function scores of participants in the intervention and control arms 6 months after the end of treatment.

Secondary outcomes will include measures of self-esteem, posttraumatic stress symptoms, social support, stigma, alcohol use, ART adherence, viral load, number of disability days, asset possession indices, and cost-effectiveness data. Primary outcomes, secondary outcomes, and all subgroup analyses will be analyzed by ITT using a multilevel mixed model adjusting for clustering in health centers to determine effect modifiers [49]. The status of randomization (intervention/control) and baseline depression score will be included as a covariate. To account for the clustered design, we will treat clusters as a random effect. Potential confounding variables (eg, age, gender, socioeconomic status) with significant differences across intervention and control arms will be included as fixed factors. The R statistical software will be used to conduct all analyses [50]. A process evaluation using mixed methods to assess acceptability, feasibility, fidelity, causal mediating processes, and contextual influences in the trial will be conducted.

The primary analysis will follow ITT principles and use all available follow-up data, with missing data handled directly through maximum likelihood estimation in mixed modeling. We will document the extent and pattern of missing data and the reasons and will conduct sensitivity analyses of the impact of missing data on stability of the primary results. Missing values will be imputed with multiple imputations. We will verify that mixed model‒based results are not sensitive to violations of model assumptions with permutation tests.

Last, Cohen *d* effect sizes will be computed for the effect estimates to determine the size of the intervention effect [51].

For the qualitative data, interview transcripts will be reviewed for accuracy and then transcribed verbatim before translation into English. To control for errors in translation, two research assistants fluent in English and the local language (Luo) will work together to translate and electronically transcribe the data [52]. QRS NVivo 10 qualitative data analysis software will be used for coding and thematic analysis [53].

The interview data will initially be coded according to a number of themes that corresponded to the focus questions. The codes will be used to construct matrix displays based on the co-occurrence of codes and the two treatment groups. The resulting matrix display will provide both the frequency of responses and the detailed content of responses, allowing us to assess how often responses varied between the two treatment groups. Intercoder reliability will be assessed.

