In a recent review of studies documenting the effectiveness of psychological interventions for PLWH in low- to middle-income countries, none of the studies that met criteria for inclusion in the review demonstrated the use of a task-shifting approach in the delivery of the intervention [14]. In a recent review of studies describing mental health training of health care workers in Africa, only three of the 37 studies reviewed described training of lay health workers (LHWs) [15]. There is a need for information on how a task-shifting approach can be used to make a psychological intervention for depression accessible and sustainable in low-resource settings.

The shifting of mental health‒related tasks from health professionals to LHWs has been repeatedly documented in non-HIV populations [16-19]. However, because mental health has not been integrated into HIV care in sub-Saharan Africa, little is known about the effectiveness of task shifting of mental health‒related services such as depression care. Also, identifying mediators and moderators of intervention response is a critical step in understanding the mediating causal factors as well as for whom and under which conditions an intervention is most beneficial [20]. This knowledge also has important implications for practice, as it can aid in tailoring and modifying interventions so as to be maximally effective for specific target populations.

To address this knowledge gap, we set out to conduct a cluster randomized trial to test the effectiveness of group support psychotherapy (GSP) delivered by trained LHWs. The recommended methodological approach to establish the efficacy of a newly developed therapy such as GSP is to first compare the therapy against a comparison group that omits the unique ingredients of the new therapy while possessing the common factors (eg, therapeutic alliance) in equal measure [21]. Thus, we compared the effects of GSP to those of group HIV education (GHE) delivered by trained LHWs on mild to moderate depression and functioning among PLWH attending primary care health centers in northern Uganda. We hypothesized that compared with the control arm, the proportion of participants that meets the Mini International Neuropsychiatric Interview (MINI) criteria for major depression will be lower and the function scores will be higher in the intervention arm 6 months after the end of treatment.

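### Two primary outcomes are named but the trial is sized for one, and the protocol does not say whether one or both must succeed

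*Protocol article*

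**What the plan says.** Two outcomes are called primary. The Statistical Analyses section reads "Primary outcomes will be the difference in follow-up proportions of participants who meet MINI criteria for major depression and difference in follow-up function scores", assessed 6 months after treatment ends. The abstract says the same, and Table 1 lists both under its primary outcomes heading. The Introduction puts them into one hypothesis: the proportion meeting criteria for "major depression will be lower and the function scores will be higher in the intervention arm 6 months after the end of treatment".

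The Sample Size and Power Calculations section has one objective: "Primarily, our objective is to compare the proportion of subjects with mild to moderate depression in the intervention and control arms". The design is said to have "80% power of detecting a 10% reduction in major depression cases at the 5% significance level". Table 2 gives proportions only. For function, Table 1 names the instrument, but no effect size, standard deviation or clustering value appears anywhere. The increase from 12 to 15 clusters per arm is explained by the multilevel models, and the increase from 32 to 40 participants per cluster by 20% loss to follow-up. Neither is attributed to a second primary outcome.

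The Conclusions refer to a primary hypothesis in the singular. No section ranks the two outcomes, divides the significance level, or says what pattern of results confirms that hypothesis.

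**The concern.** The sections do not describe the same primary question. One sizes the trial for a single comparison; the others declare two. Which error rate and which power apply depends on a rule that the article does not state.

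The practical risk is a split result, with one outcome significant and the other not. The article does not say whether that confirms the primary hypothesis, and the choice could then be made after the data are seen. This matters because the Conclusions say that confirmation, with supportive secondary data, can inform national dissemination of the intervention. It is also pressing: by the Retention section the 6-month assessments are done, and by the Results section their analysis is in progress.

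**Working it through.** **Inputs from Sample Size and Power Calculations and Table 2.** Control proportion p0 = 0.25, intervention p1 = 0.15, between-cluster coefficient of variation k = 0.25, α = 0.05, 12 clusters per arm, m = 32 per cluster (12 × 2 × 32 = 768). Planned: 15 clusters per arm, 40 enrolled, 40 × 0.8 = 32 evaluable. Sidedness is not stated; two-sided reproduces the table. The section says mild to moderate depression in its objective and major depression in its power statement; I take both to mean the MINI outcome.

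**Step 1: the plan's own figure.** Unmatched Hayes–Moulton formula for proportions:

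V = p0(1−p0)/m + p1(1−p1)/m + k²(p0² + p1²) = 0.1875/32 + 0.1275/32 + 0.0625 × 0.085 = 0.00586 + 0.00398 + 0.00531 = 0.01516

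Power = Φ(√[c(p0−p1)²/V] − z)

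At c = 12: √(12 × 0.01/0.01516) = 2.814, and 2.814 − 1.960 = 0.854, so power is 0.803. This matches Table 2, as do its other seven rows. The match needs the formula without its small-sample term, which adds one cluster per arm; with that term, power at 12 clusters is 0.769.

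**Step 2: depression power in the planned design (c = 15, m = 32).**

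| α for depression | Without the added cluster | With it (c − 1 = 14) |
|---|---|---|
| 0.05 | 3.146 − 1.960 = 1.186, so 88.2% | 3.039 − 1.960 = 1.079, so 86.0% |
| 0.025 (equal split) | 3.146 − 2.241 = 0.905, so 81.7% | 3.039 − 2.241 = 0.798, so 78.8% |

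With the 1140 recruited and 20% loss (1140 × 0.8/30 = 30.4 per cluster), the α = 0.025 figures are 80.3% and 77.3%.

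**Step 3: either outcome counts, each tested at 5%.** Under no effect on either outcome and independence, family-wise error is 1 − 0.95² = 9.75%. With correlated test statistics (bivariate normal) it is 9.5% at correlation 0.3, 9.1% at 0.5, 8.4% at 0.7 and 7.0% at 0.9.

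**Step 4: both outcomes required.** The chance of a false claim is at most 5% without adjustment. Joint power cannot exceed that of the depression test. Function power has to be assumed. Taking depression at 86.0%:

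| Assumed function power | Correlation 0 | 0.5 | 0.9 |
|---|---|---|---|
| 80% | 0.860 × 0.80 = 68.8% | 72.7% | 77.9% |
| 90% | 0.860 × 0.90 = 77.4% | 80.1% | 84.1% |

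Starting from 88.2% instead, the independent-case values are 0.882 × 0.80 = 70.6% and 0.882 × 0.90 = 79.4%.

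**The case against.** The best defence has three parts.

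First, the article claims 5% and 80% only for depression, and there the figures are right. It claims no power for function or for a joint test. This stands. A reader might infer that either the 5% error rate or the 80% power must fail. The documents do not support that. Even an equal split of the significance level leaves depression power at 81.7% in the planned design by the article's own formula, or 78.8% with the small-sample term, so error control and roughly 80% depression power can coexist. It falls clearly short, to 71.6% by the article's formula, only in the 12 × 32 calculation, which is not the planned design.

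Second, the Introduction joins the outcomes with "and" in one hypothesis, and the Conclusions use the singular. Read that way, both are required and there is no inflation of error. This is a fair reading, and no section says that either outcome alone would suffice. But the sample size section then powers only one half of the hypothesis, and its own wording points to a different reading, with depression alone as the main objective.

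Third, testing order and multiplicity are usually set out in a statistical analysis plan, which may exist. That is accepted, and the absence of a procedure is not itself the point. The point is that the article declares two primary outcomes in some sections and one primary objective in another. A separate plan could supply a rule but would not remove that conflict.

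**Conclusion.** The point holds as a conflict within the article: two primary outcomes against one sized objective, with no stated condition for success. It should be corrected, but it does not invalidate the sample size.

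Its size depends on the reading. If either outcome may count, family-wise error is 7.0–9.75% for correlations from 0.9 down to 0. If both are required, error is controlled and joint power in the planned design is about 69–78% with function power assumed at 80%, or 77–84% with 90%. The joint figures rest on those assumptions, because the article gives nothing from which function power could be computed. They also assume the plan's 25% and 15%, k = 0.25 and 32 evaluable per cluster. Power for depression alone is 86–88% at the 5% level and is not in dispute.

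**What to change.** Reconcile the hypothesis in the Introduction, the sample size section and the Statistical Analyses section with one rule: test MINI major depression first at two-sided 5%, as sized, and test function at 5% only if depression is significant. This follows the order that the sample size section already implies, holds family-wise error at 5%, and keeps depression power at 86–88%. State that the quoted power refers to the depression outcome alone.

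Date the rule before 6-month results by arm are known. The masking paragraph says that data analysts are masked, so this may still be possible; if results by arm have already been seen, say so. If an analysis plan already contains a rule, cite it with its date and bring the article's wording into line.

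The change takes a few sentences and no additional participants. The cost is that function cannot be claimed as confirmatory if depression is not significant. Requiring both outcomes would also be defensible and sits closer to the Introduction's wording, but joint power would then have to be justified with stated inputs for function.

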**Primary outcomes**								
	Major depression	The Mini International Neuropsychiatric Interview [32]	✓		✓	✓	✓	✓
	Functioning level	5-item locally developed function assessment method [39]	✓		✓	✓	✓	✓

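### The function-score co-primary is adjusted for baseline depression but not, except through a significance trigger, for baseline function, which costs precision and leaves non-significant imbalance in the estimate

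*Protocol article*

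**What the plan says.** The Statistical Analyses section names the second primary outcome as the "difference in follow-up function scores of participants in the intervention and control arms 6 months after the end of treatment". It then gives a single specification: "Primary outcomes, secondary outcomes, and all subgroup analyses will be analyzed by ITT using a multilevel mixed model adjusting for clustering in health centers". The covariates of that model are stated: "The status of randomization (intervention/control) and baseline depression score will be included as a covariate". One further route is conditional: "Potential confounding variables (eg, age, gender, socioeconomic status) with significant differences across intervention and control arms will be included as fixed factors". The primary analysis is to "use all available follow-up data, with missing data handled directly through maximum likelihood estimation in mixed modeling", so baseline function is not described as a modelled response, and no change score is mentioned.

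Baseline function exists. Table 1 lists the "5-item locally developed function assessment method" with a tick at month 0, and Data Collection and Management schedules the primary outcomes at T0. The section on participant eligibility and recruitment says: "Each client who gave informed consent received baseline assessments with a standardized questionnaire".

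**The concern.** The article chooses a baseline covariate for all outcomes, and for function it chooses a different construct from the one being analysed. A score's own baseline value is the natural covariate for its follow-up value, and here it has been collected. Leaving it out gives up precision on a co-primary outcome for which the article states no power. It also lets a chance baseline difference between 15 and 15 health centers carry into the estimate, unless that difference is large enough to trigger the conditional clause. The same rule governs the continuous secondary outcomes. Baseline depression may be a weak substitute, because every participant met criteria for major depression at entry, which may restrict the range of that score.

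**Working it through.** **The plan's own power figure.** Table 2 concerns the depression outcome only. Inputs: 25% v 15%, k = 0.25, 32 per cluster, 5% two-sided, 80% power.

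c = (1.96 + 0.842)² × [p0(1−p0)/m + p1(1−p1)/m + k²(p0² + p1²)] / (p0 − p1)²

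= 7.849 × [0.1875/32 + 0.1275/32 + 0.0625 × (0.0625 + 0.0225)] / 0.01 = 7.849 × 0.015156 / 0.01 = 11.90, so 12 clusters per arm, with power 0.803. This matches the table. It does not depend on the point made here, and it says nothing about function.

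**Precision.** Assumed, because the documents give none of them: ICC 0.05 and a baseline-to-6-month correlation r of 0.3 to 0.6. From the article: 15 centers per arm, and 32 analysed per center (40 less 20%).

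Variance of the arm contrast, in SD units, = (2/15) × [ICC + (1 − ICC)/m]. The bracket is 0.05 + 0.95/32 = 0.0797, and the within-cluster share is 0.0297/0.0797 = 0.3725.

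- If baseline function explains only within-cluster variance, the cut is 0.3725 × r².
- If r holds at the individual and cluster levels, the cut is r².

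For illustration, a test with 80% power becomes Φ(2.80/√V − 1.96), where V is the variance ratio (1 minus the cut).

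| r | Cut, within only | Power | Cut, both levels | Power |
|---|---|---|---|---|
| 0.3 | 3.4% | 0.813 | 9% | 0.836 |
| 0.4 | 6.0% | 0.824 | 16% | 0.864 |
| 0.5 | 9.3% | 0.837 | 25% | 0.899 |
| 0.6 | 13.4% | 0.853 | 36% | 0.938 |

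The within-only column depends on the ICC. At ICC 0.01 the within share is 0.0309/0.0409 = 0.756, giving a cut of 7-27%. At ICC 0.10 it is 0.0281/0.1281 = 0.220, giving 2-8%.

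**Beyond the depression score.** Assume baseline depression correlates −0.1 to −0.3 with follow-up function and −0.1 to −0.5 with baseline function, and let r hold at both levels. Adding baseline function then cuts the standard error by 2-4% at r = 0.3 and 9-15% at r = 0.5. With no depression score in the model the cuts are 5% and 13%. In all but one of the combinations tried, the depression score already takes part of the gain.

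**Imbalance.** The article reports 1140 recruited, or 38 per center and 570 per arm if equal. The SD of the chance baseline difference between arms is √{(2/15) × [ICC + (1 − ICC)/38]}. At ICC 0.05 this is √(0.1333 × 0.075) = 0.10 SD; at ICC 0.01 and 0.10 it is 0.07 and 0.13.

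Suppose the conditional clause is applied to baseline function with a t test that ignores clustering. It triggers above 1.96 × √(2/570) = 0.116 SD. The difference stays below that in about 91%, 75% and 63% of randomizations at ICC 0.01, 0.05 and 0.10. A difference just below the trigger leaves r × 0.116 in the estimate: 0.03 SD at r = 0.3 and 0.06 SD at r = 0.5.

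**The case against.** The article does not say that baseline depression is the only covariate, and an unseen analysis plan may list covariates by outcome. This carries limited weight: the article does not leave covariates open but states which ones go into the model for all outcomes, and gives one conditional route to others.

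That route has an open list of examples (age, gender, socioeconomic status), so baseline function might qualify. This part stands. A reader might infer that any arm difference in baseline function passes into the estimated effect; the documents do not support that, because a large difference could trigger adjustment. The clause limits the harm without removing it.

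A reader might also infer bias. Under chance imbalance the estimate is unbiased on average over randomizations, and its standard error already reflects that variation. Health centers were allocated before participants were recruited, so differential recruitment is conceivable, but nothing in the article shows that it occurred.

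It is tempting to quote only the 9-36% variance cut, or 84-94% power. That is the favorable end: it needs the correlation to hold between centers as well as within them. The 80% starting point is not a stated power for function either. A low correlation is plausible, since all participants were depressed at entry and only 15-25% are expected to be so at 6 months.

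For the secondary outcomes, the Introduction speaks of greater increases and reductions, which may imply some use of baseline values. The analysis section does not provide for it.

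**Conclusion.** The point holds as a loss of efficiency and conditional balance in a stated rule. The function co-primary has no unconditional adjustment for its own baseline, although the data are collected, and the significance-triggered clause is a poor substitute. Under r = 0.3-0.6, ICC 0.05 and 32 per cluster, the forgone variance reduction is about 3-13% if only within-cluster variance is explained and 9-36% if r holds at both levels, before netting out the depression score. An illustrative 80% power would become about 81-85% or 84-94%. At r = 0 nothing is lost. The reading of the text is secure; the size is not, because SD, ICC and correlation are all absent from the article. The omission does not invalidate the analysis, but it is worth correcting.

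**What to change.** State that the function model adjusts for baseline function score in addition to the baseline depression score, and that each continuous secondary outcome with a baseline measurement adjusts for its own baseline value. Do this regardless of any observed baseline difference between arms.

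No new data are needed. The cost is procedural: the article reports that analysis of baseline and 6-month data is in progress. The change should therefore be recorded and dated while the analysts are still masked. If that is no longer possible, report the baseline-adjusted model as a labelled sensitivity analysis beside the planned one.
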